### Plans to give access to the full protocol, participant-level data, and statistical code {31c}

The datasets analyzed during the current study will be available from the corresponding author on reasonable request.

## Oversight and monitoring

### Composition of the coordinating center and trial steering committee {5d}

The monitor team will visit every study site biannually to ascertain that all aspects of the program are being followed and that the trial is being carried out in accordance with the provisions of the drug clinical trial quality management practices (GCP). There are three research centers in the study. Each research center includes at least three main investigators and one coordinator. Clinical research coordinators will be responsible for registering information, obtaining informed consent, and keeping in contact with participants to inform them about treatment procedures. The investigators are experienced doctors who will perform examinations and interventions for the patients. A supervisory team of three experienced doctors will be established to assess and manage the adverse events. The data processing team includes two orthodontists who will perform the localization and UA measurements and three statisticians.

### Composition of the data monitoring committee, its role and reporting structure {21a}

A data monitoring committee is not applicable. Intervention measures in the study are well established and commonly used treatment methods, with almost no safety problems.

### Adverse event reporting and harms {22}

Adverse events will be recorded and reported by researchers within 24 h. A supervisory team of three experienced doctors from every research site will be established to assess and manage the adverse events. Serious adverse events will be reported to the Ethics Committee. For subjects in the drug and surgical treatment groups, the observation time for reporting adverse events will be from M 0 to M 7; for subjects who receive orthodontic treatment, the observation time will be from M 0 to the end of orthodontic treatment. Participants may quit the study at their guardians’ discretion or defer to the supervisory team. Circumstances that will suspend participants from study include adverse events and detection of evidence that may influence the outcomes of research. Furthermore, subjects who leave the study will be followed up until they are in stable status.

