### Trial design {8}

This study will be a multicenter and randomized controlled pilot trial. Clinical research coordinators will explain the purpose and the procedure of this study to potential subjects. The participants will undergo a series of medical tests, which will include physical examinations, maxillofacial radiography, and polysomnography, to verify the diagnosis of OSAHS and malocclusion. Subjects will be randomly divided into one of four groups—the drug treatment group, the surgical treatment group, the orthodontic treatment group, or the surgery and postoperative orthodontic group—at a ratio of 1:1:1:1. Regardless of group assignment, tests will be conducted on each group before the treatment (M 0), 7 months after the treatment (M 7), 12 months after the treatment (M 12), and 24 months after the treatment (M 24). Figure 1 shows the flow chart of the research, and Table 1 shows the clinical trial schedule.

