**Fig. 1 Fig1:**
[figure not shown]
Flow chart of study design

**Table 1 Tab1:** Schedule of enrollment, interventions, and outcome assessment

Action/timepoint	Enrollment	Baseline survey (M 0)	Randomization	Treatment	Follow-up (M 7)	Follow-up (M 12)	Follow-up (M 24)
Informed consent	⚪						
Demographic characteristics	⚪						
Medical history	⚪						
Physical examination	⚪						
Questionnaire (OSA-20)	⚪						
Lateral cephalometrics		⚪			⚪	⚪	⚪
Polysomnogram		⚪			⚪	⚪	⚪
Confirm suitability for study		⚪					
Allocation			⚪				
Drug treatment				⚪			
Surgical treatment				⚪			
Orthodontic treatment				⚪			
Surgery and postoperative orthodontic treatment				⚪			
Assessment							
Symptom changes					⚪	⚪	⚪
Questionnaire (OSA-20)		⚪			⚪	⚪	⚪
Cephalometric measurements		⚪			⚪	⚪	⚪
Morphologic analysis of UA		⚪			⚪	⚪	⚪
Polysomnogram		⚪			⚪	⚪	⚪
Safety assessment					⚪	⚪	⚪

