### Intervention description {11a}

All subjects will receive different treatments, i.e., drug treatment, surgical treatment, orthodontic treatment, and surgery or postoperative orthodontic treatment, within 4 weeks after randomization. The practitioners will be doctors who have a minimum of 5 years of work experience in their hospital and have undergone training in the trial protocol prior to the study. The training mainly includes information on the recruitment and randomization of subjects, the standardized treatment procedures, the completion of the case report form (CRF), and the adverse event reporting system.

Drug treatment group: Patients in this group will receive mometasone furoate aqueous nasal spray once a day (0.1 mg) in the morning for 2 months. The research assistants will interview the participants’ parents by telephone to remind the patients of the treatment stage.

Surgical treatment group: Patients in this group will receive AT under general anesthesia. Routine follow-up will be conducted 2 weeks after surgery to evaluate the surgical effects and the prognosis.

Orthodontic treatment group: Patients in this group will receive orthodontic treatments. They will receive orthodontic treatment according to a consistent comprehensive protocol, which mainly involves the use of a removable twin-block appliance combined with RME (see Fig. 2).

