### Outcomes {12}

Endpoint measurements will be performed before the treatment (baseline survey; month 0) and at 7 months (M 7), 12 months (M 12), and 24 months (M 24) after the starting point.

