### Concealment mechanism {16b}

The Central Randomization System can be used for the management of participant information and randomization. Prior to signing an informed consent form, this study will be fully explained to subjects and their guardians by researchers at every study site. The basic information of patients will be registered into the Central Randomization System by research assistants. After the baseline survey, the eligible participants will be divided into four groups at random with a ratio of 1:1:1:1.

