## Statistical methods

### Statistical methods for primary and secondary outcomes {20a}

Statistical analysis will be conducted using IBM SPSS Statistics (version 22.0). Descriptive analysis will be performed for all of our variates. The analysis set will consist of the intention-to-treat (ITT) set, per protocol (PP) set, and safety set. All subjects will be included in the ITT set after randomization regardless of whether they received the treatment or not. Subjects who complete treatment sessions (M 0 to M 7) without any major violation to the trial procedure will be included in the PP set. Participants who receive treatment will be included in the safety set for safety analysis. The significance level will be set so that *P* < 0.05 will be considered significant.

The primary endpoint of this study is the change in AHI from M 0 to M 7. Intergroup comparisons will be performed using an analysis of covariance (ANCOVA) to adjust for gender, obesity status, and baseline AHI. The outcomes will be mainly analyzed using the PP set. Linear regression will be used to evaluate the correlation between observed differences of AHI and the potential prognostic factors, such as gender, BMI, neck size, and research site.

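### Adverse events are observed for a length of time that depends on the allocated arm, which does not agree with the safety assessments in Table 1

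*Protocol article*

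**What the plan says.** The protocol article, section {22} (adverse event reporting and harms), sets two observation periods. The first is: "For subjects in the drug and surgical treatment groups, the observation time for reporting adverse events will be from M 0 to M 7". The second is: "for subjects who receive orthodontic treatment, the observation time will be from M 0 to the end of orthodontic treatment". By its wording the second covers the orthodontic group and also the combined group, whose children have surgery followed by an appliance.

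Section {11a} describes the orthodontic protocol as one "which mainly involves the use of a removable twin-block appliance combined with RME". Neither there nor elsewhere does the article give its duration or say what marks its end. The same section gives the drug course as 2 months.

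Table 1 has a row "Safety assessment" marked at M 7, M 12 and M 24. No row or mark in the follow-up columns is restricted to an arm. Section {8} applies the same test schedule to every group, and section {12} places endpoint measurements "at 7 months (M 7), 12 months (M 12), and 24 months (M 24) after the starting point".

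On analysis, section {20a} says: "Participants who receive treatment will be included in the safety set for safety analysis". Allocation is 1:1:1:1 (section {16b}).

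**The concern.** How long a child is watched for adverse events is fixed by the arm to which the child is randomised. An event at month 10 falls outside observation in a drug or surgery child, but inside it in a child still wearing an appliance. Differences in recorded harms then mix the effect of treatment with the length of the window.

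The clearest case is surgery alone against surgery plus orthodontics. Both groups have the same operation, and the contrast should show what the appliance adds. Under {22} it would also show what a different observation period adds.

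This matters because the Discussion says the trial will examine the disadvantages as well as the advantages of the treatments. Section {21a} also provides for no data monitoring committee, so routine event recording carries more of the safety information. Events that are never recorded cannot be recovered by a later analysis plan.

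**Working it through.** The article states no figure on this point, so there is none to reproduce. The main check sets the sections side by side.

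**Step 1. Windows by arm** (months from the start of treatment)

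| Arm | Event observation, {22} | Safety assessment, Table 1 |
|---|---|---|
| Drug | 0 to 7 | 7, 12, 24 |
| Surgery | 0 to 7 | 7, 12, 24 |
| Orthodontics | 0 to end of treatment (length not given) | 7, 12, 24 |
| Surgery plus orthodontics | 0 to end of treatment (length not given) | 7, 12, 24 |

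The last column takes Table 1 at face value, as one schedule for all arms. Read that way, two of its three safety assessments fall after observation has closed in the drug and surgical arms.

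**Step 2. Follow-up outside the window.** 24 − 7 = 17 months, and 17/24 = 71%. This applies to two arms of 352/4 = 88 children each, so 176 children.

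**Step 3. Is the window tied to treatment exposure?** The drug is given for 2 months but observed for 7. Surgery alone and surgery plus orthodontics share the operation but not the window. The rule does not follow exposure consistently.

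**Step 4. Illustration of size.** Assumptions, none of them from the article: the same constant hazard in every arm, and a risk p7 of 5%, 10% or 20% by month 7. The risk over T months is 1 − (1 − p7)^(T/7). For p7 = 10% and T = 12 this is 1 − 0.90^(12/7) = 16.5%, a ratio of 1.65 to the 10% seen in an arm closed at month 7.

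| p7 | T = 12 | T = 18 | T = 24 |
|---|---|---|---|
| 5% | 8.4% (ratio 1.68) | 12.4% (2.47) | 16.1% (3.23) |
| 10% | 16.5% (1.65) | 23.7% (2.37) | 30.3% (3.03) |
| 20% | 31.8% (1.59) | 43.7% (2.18) | 53.5% (2.67) |

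The true ratio is 1.0 throughout. A course of exactly 7 months gives no distortion. A shorter one reverses it: with T = 5 and p7 = 10%, 1 − 0.90^(5/7) = 7.2%, a ratio of 0.72. Over a window common to all arms the expected ratio is 1.0.

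**The case against.** The strongest reply has five parts.

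- **A comparison is still possible.** Events are reported within 24 hours and so should carry dates. If every appliance course lasts at least 7 months, all four arms share months 0 to 7. This stands: a reader might infer that harms cannot be compared at all, and the article does not support that. It also does not secure the comparison, because the course length is not given.
- **No crude comparison is announced.** The endpoints are efficacy measures, and the choice of safety analysis can be left to an analysis plan. This also stands, so the missing exposure adjustment is not the point. The point is the collection rule itself, since no analysis plan can restore unrecorded events.
- **The direction is unknown.** A reader might infer that the rule always counts against the orthodontic arms. That holds only if courses run past month 7. Section {20a} defines the per-protocol set by treatment sessions from M 0 to M 7 without distinguishing arms, which is compatible with a course of about 7 months and little difference between windows.
- **The window follows exposure.** Harms of a short drug course or a single operation would be expected mostly before month 7, and a constant hazard suits them poorly. This weakens the illustration, which at most describes background events. It does not rescue the rule, for the reasons in step 3.
- **Table 1 may be a merged schedule.** Its later safety marks could be meant only for children still in orthodontic treatment, or for something other than event reporting. That is possible, so this is a disagreement to reconcile and not a proven contradiction. The article, however, gives no such definition or restriction.

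**Conclusion.** The point holds in a limited form. Section {22} makes event observation time depend on the allocated arm, and this does not agree with Table 1 as printed. Crude counts or proportions over these windows are not like for like. If {22} governs, events in months 7 to 24 after drug or surgery are not captured. These conclusions rest on the text alone.

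The size is not known. The ratios of about 1.6 to 3.2 rest on an assumed event rate, an equal constant hazard, and courses of 12 to 24 months that the article does not state. They show what the rule could do and are not estimates for this trial. The matter should be corrected, but it does not touch the primary endpoint.

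**What to change.** Reconcile section {22} with Table 1 by recording adverse events in all four arms over at least M 0 to M 24. Continue beyond M 24 for any child still in orthodontic treatment, so that the change shortens nobody's observation. State what marks the end of orthodontic treatment for this purpose, and say what the safety assessment in Table 1 consists of. Compare arms only over common periods, M 0 to M 7 and M 0 to M 24, and describe later events in the orthodontic arms separately.

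The cost is a change of wording, plus event recording and 24-hour reporting for 17 more months in the drug and surgical arms. The visits to M 24 (sections {8} and {12}) and the monthly contacts with participants (section {18b}) are already planned. For children already past M 7 in those arms, later events would have to be sought retrospectively, and the report should say so.

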### Frequency and plans for auditing trial conduct {23}

The monitor team, consisting of people from the sponsor Shanghai Hospital Development Center, will visit every study site biannually to ascertain that all aspects of the program are being followed and that the trial is being carried out in accordance with the provisions of the drug clinical trial quality management practices (GCP). During the monitoring visit, the monitor will check the CRFs for subjects in the trial to confirm that all items have been completed and that the data are being obtained according to the protocol. The monitor will also check that the CRF data are consistent with the clinical record or the original data.

### Plans for communicating important protocol amendments to relevant parties (e.g., trial participants, ethical committees) {25}

During the study, there may be program modifications that may affect the study or patient safety. Any modifications shall be agreed upon by the sponsor/researcher and the Ethics Committee prior to their implementation. Revisions shall be recorded in a new written version, which must be signed by the same parties who signed the final draft of the pilot protocol.

### Dissemination plans {31a}

The final clinical report will be the basis for the study to be published in a medical journal or reported at conferences. A formal report or publication of the data from the study will be jointly published by a person appointed by the principal investigators.

## Discussion

Cranial and maxillofacial growth and development in children are influenced by both genetic and environmental factors [46]. The change of respiratory mode in children may alter the oropharyngeal muscle tone, which affects the development of maxillofacial sections. Mouth breathing is one of the main clinical symptoms of OSAHS in children, and it is common to find facial features such as long faces, maxillary constriction, high arched palates, and mandibular retrognathia among mouth breathers [28, 30]. The contraction of the upper airway (UA) is closely related to this kind of maxillofacial deformity, while maxillofacial deformities can also be the primary or promoting factor for OSAHS. The longer mouth breathing continues and the more serious the skeletal alterations that occur in OSAHS children, the more difficult it will be to cure the OSAHS. Therefore, early diagnosis of the morphologic analysis of the UA and maxillofacial structure is crucial for pediatric OSAHS. In this study protocol, CBCT of subjects will be performed for both morphologic analysis of the UA and cephalometric measurements to assist in diagnosis and efficacy evaluation. Traditional and commonly used efficacy evaluation methods in pediatric OSAHS such as PSG and the OSA-20 questionnaire are also included in this study.

Although new treatment patterns have recently been proposed, treatment methods for children have continued to be particularly challenging [26]. Furthermore, there is still great controversy concerning the treatment of OSAHS in clinic due to the lack of randomized controlled studies comparing treatment approaches. In this study, a multicenter randomized controlled trial was designed to investigate the advantages and disadvantages of AT and/or orthodontic treatment for children with mild OSAHS and mandibular retrognathia.

This study protocol still faces several limitations and challenges. The first is the challenge of sample selection of children with mild OSAHS and mandibular retrognathia. Due to the limited acceptance of randomization, it may take a long time to collect the sample size required for this study. The second is the challenge of subjects’ compliance. Additional services will be provided for participants through WeChat or phone to arrange treatment times and enhance adherence. The third limitation is the consistency of treatment. Before the study begins, all of the surgical and orthodontic treatment teams will receive specific training on the normalized research procedure to ensure consistency.

The results of this study will provide valuable evidence for the merits and long-term efficacy of different treatment approaches and contribute to facilitating the multidisciplinary treatment of pediatric OSAHS.

## Trial status

The study has been ongoing from May 2018. Recruitment is expected to be completed by the end of December 2021. The protocol version is 1.0 (issue date 17 November 2017).

## Abbreviations

AHI: Apnea/hypopnea index
AI: Apnea index
AT: Adenotonsillectomy
BMI: Body mass index
CBCT: Cone beam computed tomography
CPAP: Continuous positive airway pressure
CRA: Clinical research assistant
CRF: Case report form
HI: Hypopnea index
ITT: Intention-to-treat (set)
LSaO_2_: Lowest oxyhemoglobin saturation
MAD: Mandibular advancement device
OSAHS: Obstructive sleep apnea/hypopnea syndrome
PP: Per protocol (set)
RME: Rapid maxillary expansion
